# IDTWO: A Protocol for a Randomised Controlled Trial of a Web-Based Mental Health Intervention for Australians with Intellectual Disability

**DOI:** 10.3390/ijerph18052473

**Published:** 2021-03-03

**Keywords:** intellectual disability, electronic mental health, RCT, CBT, mental health promotion

## Abstract

People with intellectual disability (ID) experience higher rates of mental illness and reduced access to appropriate care and treatment. Tailored electronic mental health (eMH) programs offer opportunities to address these disparities. The aim of this study is to examine whether a fully automated and self-guided eMH program tailored to the needs of people with ID can reduce symptoms of anxiety and depression and improve daily functioning in people with borderline-to-mild ID. Australians with borderline-to-mild ID, aged 16 years and older with mild-to-moderate depression and/or anxiety symptoms will be eligible to participate with the help of a nominated carer, if necessary. A randomised controlled trial with a sample size of 150 participants divided into treatment and waitlist control arms will be conducted. Participants randomised to the intervention group will have full access to the Healthy Mind program for eight weeks. The waitlist control group will gain full access to the program following the eight-week treatment period. Efficacy will be assessed on the Anxiety, Depression, and Mood Scale; Kessler-10; and the World Health Organisation Disability Assessment Schedule 2.0 across three time-points (baseline, eight weeks, and three months). We expect that people who use the intervention will report reduced depression and anxiety, relative to the control group. To our knowledge, this is the first study to examine the effectiveness of a fully automated eMH program for improving mental health in people with ID. We expect our study to render new knowledge on the delivery and effects of internet-based cognitive behaviour therapy (CBT) tools for people with ID.

## 1. Introduction

People with intellectual disability (ID) urgently need access to better mental healthcare [1]. Mental illness rates in this group are estimated at 2–3 times those of the general population [2,3]. Despite this prevalence, relatively few access appropriate mental health services [4]. Overlap between the cognitive and behavioural features of ID and common symptoms of mental illness can lead to diagnostic overshadowing [3,5,6,7]. Thus, symptoms of mental illness are often not properly identified, and the need for tailored or specialised mental health intervention may be underestimated.

People with ID who need mental health support face numerous barriers to accessing services [8]. ID itself poses a barrier to traditional therapies, which are designed and evaluated in neurotypical individuals [9,10], and many clinicians feel they lack the ability or training to provide appropriate care [11], which is important for effective engagement [12]. Talking to healthcare professionals can be daunting, with some individuals with ID opting to avoid physicians whenever possible [13]. People with ID are more likely to come from low-socioeconomic areas, which is both a barrier to services and a risk factor for poor mental health [3]. Australian mental health services for people with ID lag behind international best-practice guidelines [4], and they are poorly represented in mental health policy-making [14]. Though the National Disability Insurance Scheme (NDIS) offers funding for much-needed disability-related support for Australians with ID, concerns remain about the availability of appropriate mental health supports, which must be accessed through mainstream health services [15].

The impact of poor mental health in ID begins early in life. Despite experiencing higher rates of mental illness than their peers, only 1 in 10 young Australians with ID and mental illness (age rage = 5–19.5 years) receive adequate mental health care [16]. School drop-out rates for youth with ID are around one-in-three, and 50% of those who drop out cite behavioural or emotional difficulties as the primary reason [16]. Adolescence is also a time of psychiatric vulnerability [2,17] and substantial cognitive development [18,19].

Mental health has life-long implications for people with ID. Joining the workforce or living away from home for the first time are pivotal moments in early adulthood. These life transitions can be difficult for people with ID [20]. Young people with ID worry about life transitions more than their neurotypical peers, and this worry is primarily focused on coping with psychosocial distress [21]. Nevertheless, successful coping during life transitions appears to be an important factor in the long-term functioning of people with ID [22]. The ability to work and participate in their community can have wide-ranging health benefits [23]. Promoting autonomy in people with ID can help them improve problem-solving skills and feel less anxious when faced with new challenges [22]. Carers may also experience benefits to their psychological well-being [23]. The potential for wide-ranging benefits further emphasises the importance of creating accessible mental healthcare options for people with ID.

Electronic mental health (eMH) can potentially deliver tailored cognitive behaviour therapy (CBT) to thousands living with ID. This type of intervention is also uniquely placed to address many of the recommendations for adapting CBT for people with ID, such as shortened sessions, appropriately simplified language, highly visual activities, and tools that are easy for carers to use and be involved with [24,25]. eMH tools are scalable, effective, and engaging [26,27,28]. By necessity and design, online therapies are visual and interactive. The length of modules can be varied, and the time spent on each module is easily managed by the individual. Being simple and accessible, carers can easily familiarise themselves with the content and have the tool readily at hand. Effective eMH programs could also be used as an adjunct to traditional face-to-face therapy, with computer-based therapy tools improving engagement and therapeutic alliance for some clinicians and service users [13].

The present paper describes a randomised controlled trial (RCT) named the Intellectual Disability Trial for Well-being Online (IDTWO). IDTWO will evaluate the efficacy of the eMH tool Healthy Mind (Black Dog Institute, Sydney, Australia) in people with borderline-to-mild ID and mild-to-moderate symptoms of anxiety and/or depression. To our knowledge, Healthy Mind is the first self-guided and fully automated ID-specific eMH program designed in consultation with ID experts and lived-experience consultants. Healthy Mind is based on myCompass (Black Dog Institute, Sydney, Australia), an established eMH program that helps users alleviate the symptoms of depression while improving their psychosocial functioning [29]. This paper was prepared using the SPIRIT checklist for presenting clinical trial protocols and the CONSORT-EHEALTH checklist [30,31].

## 2. Objectives and Hypotheses

The primary aim of this study is to answer the research question regarding whether using a tailored eMH program (Healthy Mind) can reduce symptoms of anxiety and depression and improve daily functioning in people aged 16-years and over with borderline-to-mild ID. A secondary aim is to examine any effects that specific impairments in intellectual functioning (e.g., poor working memory) may have on engagement with, and benefits of, an eMH program. We predict that people who use the intervention will report reduced depression and anxiety, relative to the control group. We also predict that lower scores on tests of cognitive function will be related to lower engagement and benefit in the treatment group.

## 3. Trial Design

The study described here is a two-arm individually randomised controlled trial (RCT) conducted wholly online. Participants allocated to the intervention group will have full access to the Healthy Mind program for 8 weeks. Participants randomised to the control group will be placed on a waitlist for 8 weeks and given full access to the Healthy Mind program after their waitlist period expires. Participants in both groups will have uninterrupted access to treatment as usual for the duration of their study participation.

## 4. Methods

### 4.1. Participants, Interventions, and Outcomes

#### 4.1.1. Study Setting

The setting for this study is Australia. Approximately, 1–2% of the Australian population live with ID, defined as an intelligence quotient of below 70 [32,33,34,35].

#### 4.1.2. Eligibility Criteria

Participants will be eligible to participate if they are aged 16 years or over, have documented ID in the borderline or mild range, report mild-to-moderate symptoms of depression and/or anxiety, and are computer and internet literate. In addition, each study participant will be required to nominate a trusted carer to provide support throughout all trial stages. Consent, screening, and all other data collection will be completed online with carer support.

Participants will be ineligible if they have an ID diagnosis in the moderate range or above, report severe mental health problems (severe symptoms of anxiety and/or depression, severe mood disturbance and/or mania, suicidal ideation, psychotic symptoms), or are experiencing medical comorbidities or other functional impairments that might impede trial engagement (e.g., impaired vision, hearing, motor skills, etc.). Ineligible participants will be offered the opportunity to participate in the community collaboration aspect of our dissemination plan, which will involve giving lived-experience feedback on the trial results and recommendations about how future trials and services for people with ID should be designed. Any potential participant reporting severe mental health symptoms will be referred to their general practitioner for further assessment. Participants reporting acute distress will be referred to phone services offering immediate support including, Lifeline, Kids Helpline, and the Suicide Call Back Service.

#### 4.1.3. Interventions

Active intervention (Healthy Mind): Healthy Mind (www.healthymind.org.au) is a first-of-kind, fully automated, web-based eMH program tailored to the needs of people with ID (Figure 1). Participants randomised to the active intervention condition have access to the full Healthy Mind program for 8 weeks. Healthy Mind comprises five interactive activities (Figure 2) designed collaboratively by ID consumers and experts: (1) the “Recognising feelings” activity helps users to identify and regulate negative emotions (e.g., sad, angry, and worried); (2) “Breathe and relax” helps users understand how to use controlled breathing to calm strong emotions and be more present in their everyday life; (3) “Taming anger” offers users strategies for reducing frustration and improving communication when feeling overwhelmed; (4) “Having more fun” suggests enjoyable activities involving socialising, exercise, and leisure. The activity helps users to integrate fun activities into their regular routines, using a weekly planner; and (5) the “Tackling unhelpful thinking” activity translates core aspects of cognitive therapy into simple strategies for re-appraising stressful thoughts.

Each activity is presented in easy-read English and has two sessions that follow a three-step process (Figure 3): (1) “Learn about it”; (2) “Watch it”; and (3) “Do it” [36]. At step 1, users read an introduction to the topic and explanation of its impacts and value. At step 2, users watch a brief video tutorial demonstrating what the skill or behaviour looks like, enacted. At step 3, users are presented with opportunities to practise the new skill or behaviour with guided visual or audio instructions, interactive activities, and using a worksheet available for download. The program design was developed based on user feedback, elicited during the feasibility and accessibility trial [37]. For example, users requested a highly simplified structure involving early access to the videos, which were to be presented separately to the participatory components. To further enhance accessibility, users can click an icon to hear the words on the screen read aloud throughout each activity, and an animated dog is always at hand to provide support using a chat interface. Healthy Mind also offers educational and support resources for carers and emergency contact options for users who may be experiencing significant distress.

Pilot testing of Healthy Mind revealed that a sufficiently robust password system was a barrier to access due to the different language and memory abilities of users, given the site is intended for independent use by some consumers in the future [37]. Therefore, the Healthy Mind site does not require a login. User privacy is maintained by ensuring each user session is secure and unidentifiable. This is achieved by removing all opportunities to enter identifiable information (e.g., users are never asked to provide their name or any other identifiers). Identifiable information is only entered into a separate study website (detailed below).

The absence of a login system in the intervention poses a challenge for monitoring engagement with the treatment. Although this is not ideal methodologically, our priority has been to create an accessible website. This priority was identified in our co-design process previously described in our team’s publication [37]. Treatment engagement will therefore be assessed retrospectively by self-report at the first follow-up measurement.

Waitlist control group: The control group will be advised that there will be a delay in being able to access to Healthy Mind and that they will receive an email from the research team as soon as the website is available to access (i.e., after the three-month follow-up survey has closed). Control group fidelity will be maintained by collaborating with study helpers to avoid access to Health Mind and surveying control participants after the 8-week period to ensure that they were not exposed to Healthy Mind.

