## 5. Participant Timeline

Participant consent, screening, and assessment will take place online via a secure study-specific website hosted on the Black Dog Institute research platform (https://healthymind.blackdoghealth.org.au), which is separate from the intervention site. The research platform is password-protected; therefore, participants may require support from their helper during this component of the study. Once on the secure site, potential participants and their helper will complete the online screening questionnaire to establish eligibility. Eligible participants and their helper will then each provide informed consent online by reviewing and agreeing to the participation information and consent statement. After providing informed consent, eligible participants will be directed to a secure website where they will enter contact details and complete the baseline questionnaires with support from their helper, then complete the CBS Health cognitive assessment independently. To allow for participant fatigue, all online assessments can be paused and resumed at a later date. Ineligible participants will receive automated feedback explaining that the study is not right for them, based on their answers. Details of telephone counselling support (e.g., Lifeline) and other self-help and face-to-face resources will be provided as appropriate.

After baseline assessment, eligible participants will be randomly allocated to one of two conditions using computerised block randomisation at a 1:1 allocation ratio: (1) the intervention condition, in which participants have full access to the Healthy Mind program; or (2) the control condition, in which participants are placed on a waitlist and given access to Healthy Mind at the conclusion of the waitlist period. Subsequent assessment points coincide for both groups at post-intervention (8 weeks) and 3 months after randomisation. The full flow of participants is presented in Figure 4.

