## 6. Sample Size

The primary outcomes for this study are depression and anxiety symptoms (measured using the ADAMS). Meta-analysis of psychological therapies for people with ID suggests an expected effect of treatment on similar measures of anxiety and depression symptoms of approximately 0.6 [43]. However, this is based on face-to-face treatments and may represent an overestimation [44]. To detect a more conservative effect size of ~0.5, we will need a minimum of 50 participants per group, therefore we will recruit a sample of approximately 167 individuals to allow for ~40% attrition. This calculation was based on the group differences on ADAMS between waitlist control and intervention groups at 8 weeks and 3 months, assuming 80% power and alpha = 0.05 (0.025 for each primary group difference), in order to detect a mean difference of 0.5 standard deviation units at 8 weeks and at 3 months.

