### 10.4. Ancillary and Post-Trial Care

At the conclusion of the assigned waitlist period, the active intervention will be made available to all participants in the waitlist control group.

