**Figure 4 ijerph-18-02473-f004:**
[figure not shown]
Healthy Mind CONSORT diagram.

**Table 1 ijerph-18-02473-t001:** Outcome measures completed at each measurement point.

Outcomes	Baseline	Post-Intervention (8 Weeks Post Randomisation)	Follow-Up (3 Months Post Treatment Completion)

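### The protocol gives two incompatible times for control access to Healthy Mind, and only the later one keeps the 3-month contrast free of control exposure

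*Protocol article*

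**What the plan says.** Two access times for the control arm stand in the current text of the protocol article.

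- **Week 8.** Section 3: "Participants randomised to the control group will be placed on a waitlist for 8 weeks and given full access to the Healthy Mind program" once that waitlist ends. The Abstract: "The waitlist control group will gain full access to the program following the eight-week treatment period".
- **After the last assessment.** Section 4.1.3, on the waitlist group, says controls will be emailed "as soon as the website is available to access (i.e., after the three-month follow-up survey has closed".

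Two other sections give no length. Section 5 says "participants are placed on a waitlist and given access to Healthy Mind at the conclusion of the waitlist period", and Section 10.4 says "At the conclusion of the assigned waitlist period, the active intervention will be made available to all participants".

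Section 6 bases the sample size on "group differences on ADAMS between waitlist control and intervention groups at 8 weeks and 3 months", with alpha 0.025 for each primary difference and 0.5 SD assumed at both times.

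The date of the 3-month assessment also varies. Section 5 has "Subsequent assessment points coincide for both groups at post-intervention (8 weeks) and 3 months after randomisation"; the Table 1 column heading is "Follow-Up (3 Months Post Treatment Completion".

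Section 4.1.3 adds that the intervention site has no login, that study helpers are asked to keep controls off it, and that controls are surveyed about exposure after the 8-week period.

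**The concern.** When controls get the programme decides what the 3-month difference estimates. If they get it after the 3-month survey, the difference is Healthy Mind against no Healthy Mind, on top of usual care in both arms. If they get it at week 8, the difference is immediate against delayed access. The second quantity shrinks as controls benefit, so a small 3-month difference could be misread as an effect that has worn off.

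The data could not settle the matter afterwards. Without a login there is no usage record by participant, and the only control-exposure check described comes after week 8. That leaves the interval in which the two texts differ without a stated check.

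**Working it through.** **1. The statements side by side**

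| Place | When controls get access |
|---|---|
| Section 3 | after an 8-week waitlist |
| Abstract | after the 8-week treatment period |
| Section 4.1.3 | after the 3-month survey closes |
| Sections 5 and 10.4 | end of the waitlist, length not given |

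The only waitlist length stated anywhere is the 8 weeks in Section 3. Read with that length, Sections 5 and 10.4 point to week 8, against Section 4.1.3.

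**2. Control access before the 3-month survey, if released at week 8** (3 months taken as about 13 weeks)

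- Counted from randomisation (Section 5): 13 − 8 = about 5 weeks.
- Counted from treatment completion (Table 1): (8 + 13) − 8 = about 13 weeks, longer than the 8-week intervention itself.
- Release after the survey (Section 4.1.3): 0 weeks by design.

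**3. The plan's own sample size**

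Inputs from Section 6: d = 0.5, power 80%, alpha 0.025 per difference, 50 per group, about 40% attrition. Normal approximation: n per group = 2 × [(z for alpha + 0.842) / d]².

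- Two-sided 0.025: 2 × [(2.241 + 0.842) / 0.5]² = 76.04, so 77.
- One-sided 0.05, no split: 2 × [(1.645 + 0.842) / 0.5]² = 49.5, so 50.
- Attrition: 100 / (1 − 0.40) = 166.7, so 167, as stated.

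The 50 per group is therefore not reproduced at two-sided 0.025 in a simple two-group comparison. That is a separate matter, and step 4 keeps it apart from dilution.

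**4. Illustration of dilution under the week-8 reading**

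Assumption: by the 3-month survey, controls have gained a share f of the 0.5 SD. The documents give no value, so a range is shown. The remaining contrast is d = 0.5 × (1 − f). Power is for a two-sample t-test at two-sided 0.025, with noncentrality d × √(n/2). Sidedness is assumed, since Section 6 does not state it. On the t distribution, 80% power at d = 0.5 needs 77.3, so 78 per arm.

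| f | Contrast (SD) | Power, 50 per arm | Power, 78 per arm |
|---|---|---|---|
| 0 | 0.500 | 59% | 80% |
| 0.25 | 0.375 | 35% | 53% |
| 0.50 | 0.250 | 16% | 24% |
| 0.75 | 0.125 | 5% | 7% |

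The last column isolates dilution, because it starts from the intended 80%. The f = 0 row is the Section 4.1.3 reading.

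**The case against.** The best defence is that the document leans towards the later date, so this is loose summary wording rather than an undecided design. Section 4.1.3 is the specific, operational text. Section 8.2 keeps participants blind through follow-up, which fits poorly with release at week 8. Section 10.4 places control access under post-trial care. Section 6 assumes the full 0.5 SD at 3 months. The Abstract sets no end date, since access after the survey also follows the treatment period. The participant flow figure is not shown and might give the date. This shows which reading was probably intended, but none of the visible text gives another waitlist length or corrects Section 3, which states 8 weeks outright.

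It can also be said that Section 4.1.4 names no primary time point, and that the 0.025 might be meant for the depression and anxiety subscales. Section 6 nevertheless sizes the trial on a 0.5 SD difference at both 8 weeks and 3 months, so the 3-month contrast carries design weight either way.

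Three cautions stand:

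- The control gains are assumed, and a t-test is not the planned mixed model. A baseline correlation of about 0.6, which the protocol does not state, would bring the requirement to about 49 per group, so the 59% should carry no weight here.
- Asking about exposure after week 8 does not rule out asking again at 3 months.
- If the 8-week text is what the ethics committee approved, a longer wait is more than an editorial change.

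**Conclusion.** The concern holds. Section 3 and Section 4.1.3 set different access times for the same group, and the protocol text does not reconcile them. This rests on the wording and on no calculation.

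The consequence depends on which text is followed. Under Section 4.1.3 the 3-month contrast is sound and the Abstract and Section 3 misdescribe the trial. Under Section 3, a contrast on which the trial was sized has a control arm with about 5 or 13 weeks of access, and its power could fall from 80% to between 53% and 7% over the assumed range of control gain. That range illustrates the stakes and is not an estimate. Because the choice settles what the 3-month result means, it must be fixed before that result is interpreted.

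**What to change.** - State one access time throughout: after the 3-month survey has closed. Correct the Abstract and Section 3, and give that waitlist length in Sections 5 and 10.4.
- State once whether the 3 months run from randomisation or from treatment completion, and align Section 5 with Table 1, since this sets the access date.
- Repeat the control-exposure question in the 3-month survey.

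The 3-month contrast then stays as planned. Only if access is in fact given at week 8 should the 8-week contrast become the sole primary time point, with the 3-month difference reported and labelled as immediate versus delayed access.

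**Cost.** Wording in the protocol and participant information, and one survey item; no extra participants. Compared with the 8-week text, controls wait about 5 weeks longer (3 months from randomisation) or about 13 weeks longer (from treatment completion), with usual care continuing. If the approved documents promised access at week 8, the longer wait needs an ethics amendment and may need to be put to participants again.
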